#### Statistical analysis

Data analyses will be performed by a statistician blinded to group assignments using SAS version 9.4 (SAS Institute, Cary, NC, USA). Analysis will be performed by intention-to-treat principle, with all randomly assigned participants included. Missing data will be imputed using the multiple imputation method. The primary outcome will be analyzed using analysis of covariance (ANCOVA) or Kruskal–Wallis H test, as appropriate. The ANCOVA model will include changes in the WOMAC pain score from baseline to week 2 as the dependent variable, treatment as the independent variable of interest, and the baseline WOMAC pain score and study site as covariates; when it is significant (*P* < 0.05), the Tukey–Kramer adjustment will be applied for pairwise comparisons across groups while maintaining 5% type I error rate. In case the Kruskal–Wallis H test is significant (*P* < 0.05), Mann–Whitney *U* test will be applied for pairwise comparison, and the significance level for the type I error will be adjusted by Bonferroni correction at *P* < 0.017.

For secondary outcomes, continuous variables will be assessed using ANOVA or the Kruskal-Wallis H test, as appropriate, with the same multiple comparison methods as the primary outcome; binary categorical variables will be compared using the Cochran–Mantel–Haenszel method adjusted for randomization strata.

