Moxibustion is a traditional Chinese medicine (TCM) therapy involving ignited material to apply heat to certain acupuncture points or areas of the body surface for curing disease through the regulation of the function of meridians and visceral organs [13]. Among the various materials used for moxibustion, moxa floss, a cotton-like material made from dried leaves of Artemisia argyi (a plant commonly known as moxa or mugwort) [13], has survived the test of long-term medical practice and become the most recognized version. Since mugwort is widespread throughout China, there are many habitats for commercially available moxa floss, among which Qichun County, Hubei Province, and Nanyang County, Henan Province become the two largest producers. According to the classical TCM theory, the habitat of moxa floss is crucial to the effect of moxibustion, and the best habitat is granted to Qichun County, Hubei Province. It has been reported that dried leaves of Artemisia argyi native to Qichun County, Hubei Province, produce a higher content of volatile components and a larger output of combustion heat release than those native to other habitats in China [14, 15]. However, this does not imply a similar clinical effect of moxibustion. Though moxa floss native to Qichun County, Hubei Province has been long believed to be the optimal moxibustion material by TCM practitioners, so far there are no clinical studies comparing the moxibustion effect among moxa floss from different habitats. The primary objective of this randomized controlled trial is to compare the effects of moxibustion using moxa floss from Qichun County, Hubei Province (Qichun moxa floss) versus those from Nanyang County, Henan Province (Nanyang moxa floss) in alleviating knee pain for patients with KOA, thus to determine whether the habitat of moxa floss contributes to the effect of moxibustion. The results of this study will also help to validate the effectiveness of moxibustion for KOA via the comparison between moxibustion and sham moxibustion.

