### Statistical methods

#### Sample size

There are no previous clinical studies comparing different habitats of moxa floss, or are there studies comparing moxa floss with non-moxa floss for the effect of moxibustion. Based on the results of a study investigating moxibustion versus a heat-insulated placebo moxibustion for KOA [22], we assumed a standard deviation of 10 for group C (sham moxibustion), and 12 for groups A and B (moxibustion). The sample size calculation was based on the formula of one-way analysis of variance (ANOVA) with pairwise comparisons, with 80% power, a two-sided significance level of 5% and a 15% dropout rate. We designed this study to detect: (1) a difference of 5 points in the WOMAC pain score for comparison between moxibustion using different habitat moxa floss; that is groups A and B with an allocation ratio of 1:1; and (2) a minimal clinically important difference of 10 points [23, 24] for comparison between moxibustion (group A or B) and sham moxibustion (group C) with an allocation ratio of 2:1. For the first comparison, 140 participants will be needed for groups A and B; for the second comparison, 45 participants will be needed for group C, and 90 for groups A or B. The larger result from the first comparison was then used to determine the final sample size, that is, 140 participants in groups A and B, respectively, and 70 in group C. The total sample size is 350 participants.

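### With three arms, Tukey–Kramer after a significant omnibus test is stricter than 5% family-wise control requires and gives up as much as 9 points of power for group A versus group B

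*Protocol article*

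**What the plan says.** The Background section puts A versus B first: "The primary objective of this randomized controlled trial is to compare the effects of moxibustion using moxa floss from Qichun County" with moxa floss from Nanyang. It adds that the comparison with sham will also help to validate moxibustion. The Discussion opens with both questions as the objective.

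The Sample size section uses the "formula of one-way analysis of variance (ANOVA) with pairwise comparisons", "with 80% power, a two-sided significance level of 5% and a 15% dropout rate". It assumes SDs of 12 in A and B and 10 in C, with targets of 5 points for A versus B and 10 points for either real arm versus sham. A versus B drives the total: "The larger result from the first comparison was then used to determine the final sample size". This gives 140, 140 and 70.

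The Statistical analysis section tests treatment in a three-group ANCOVA. Only if P < 0.05 are pairs examined, and then the Tukey–Kramer "adjustment will be applied for pairwise comparisons across groups while maintaining 5% type I error rate". The rank-based alternative is a Kruskal–Wallis test at 0.05 followed by Mann–Whitney tests at 0.017.

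**The concern.** Two devices for multiplicity are stacked, and for three arms either one suffices. Tukey–Kramer controls the family-wise error without a gate. A gate followed by unadjusted pairs also controls it, by closure. If all three means are equal, a false claim needs a false omnibus rejection, which has 5% probability. If exactly one pair is equal, only that pair can be falsely claimed, and it is tested at 5%. There is no other null configuration.

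At stake is power for A versus B. It is the smaller of the two targets (5 points, 5/12 = 0.42 SD) and the comparison named as the primary objective. When C clearly differs, the omnibus test is almost always significant. A versus B is then effectively tested at about 1.9%, although 5% would keep the family-wise guarantee.

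**Working it through.** **1. The plan's own sample size.** n per arm = 2σ²(z₁₋α/₂ + z₀.₈)²/δ², with σ = 12 and δ = 5, so 2σ²/δ² = 11.52.

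- α = 0.05/3: 11.52 × (2.394 + 0.842)² = 120.6, so 121. Then 121 × 1.15 = 139.2, so 140, as stated. Dividing by 0.85 gives 143.
- α = 0.05: 11.52 × (1.960 + 0.842)² = 90.4, so 91. With dropout this becomes 105 or 108, which does not match.

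The stated 140 therefore fits a correction for three pairs.

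**2. Power for A versus B, direct calculation.** After 15% loss, 140/140/70 becomes 119/119/60, with 295 residual degrees of freedom. With SD 12 throughout, SE = 12√(2/119) = 1.556 and 5/1.556 = 3.214. If the gate is passed:

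- Tukey–Kramer: the critical value on the t scale is 2.356 (two-sided tail 1.9%). Power = Φ(3.214 − 2.356) = Φ(0.858), about 80.5%.
- Unadjusted 5%: the critical value is 1.968. Power = Φ(1.246), about 89.4%.

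**3. Power by simulation.** One-way layout, at least 200,000 runs per case, A–B = 5, 119/119/60. The closed test uses pooled variance where the SDs are equal. Where they are 12/12/10 it uses separate variances (Welch form) in the gate and the pairs.

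| Position of C | SDs | As planned | Gate, then 5% pairs | Gain (points) |
|---|---|---|---|---|
| 10 points beyond B | 12/12/12 | 80.4% | 89.4% | 9 |
| 10 points beyond B | 12/12/10 | 82.4% | 89.2% | about 7 |
| Equal to B | 12/12/12 | 80.0% | 85.6% | about 6 |
| Equal to B | 12/12/10 | 82.1% | 86.0% | about 4 |
| Midway between A and B | 12/12/12 | 79.4% | 81.7% | about 2 |
| Midway between A and B | 12/12/10 | 81.3% | 81.3% | about 0 |

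With nobody lost (140/140/70, SD 12, C 10 points beyond B) the figures are 87.0% and 93.5%, a gain of 6.5 points.

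**4. Which layer costs the power.** Tukey–Kramer alone against gate plus Tukey–Kramer, SD 12: 80.4% and 80.4% with C 10 points beyond B, 80.4% and 80.0% with C equal to B, 80.5% and 79.4% with C midway. The gate costs 0 to about 1 point. The rest is Tukey–Kramer.

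**5. Family-wise error, 119/119/60.**

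| Rule | SDs | All equal | A = B, C far | A = C, B far |
|---|---|---|---|---|
| As planned | 12/12/12 | 4.4% | 1.9% | 1.9% |
| Gate, 5% pairs, pooled variance | 12/12/12 | 5.0% | 5.0% | 5.0% |
| Gate, 5% pairs, pooled variance | 12/12/10 | 4.2% | 5.8% | 3.3% |
| Gate, 5% pairs, separate variances | 12/12/10 | 5.0% | 5.0% | 5.0% |

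With pooling, the smaller SD in C pulls the common variance below 144, so the A-versus-B test runs above 5%. Separate variances remove this.

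**The case against.** The strongest defence is that the plan is coherent. Its sample size allows for a three-pair correction, its analysis applies one, and planned power after dropout is at or just above the stated 80%. A prespecified, valid and slightly conservative rule for a trial that wants to interpret all three pairs needs no apology. All of this stands, and it limits the point to efficiency.

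Four stronger readings are tempting but unsupported:

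- *The trial is underpowered for its primary objective.* It is not, on its own assumptions. The Discussion's remark that the sample size lacks strong support concerns the assumed habitat difference, for which there was no earlier study. It does not concede that the testing rule is weak.
- *The comparison is penalised twice.* The gate costs almost nothing, so dropping it while keeping Tukey–Kramer would recover about 1 point at most.
- *The gate alone guarantees 5%.* That holds with equal variances. With the plan's own SDs and a pooled variance, A versus B reaches about 5.8%.
- *A versus B should be tested first at 5%, with the sham contrasts after it.* If A and B are truly equal, that order would block formal sham comparisons about 95% of the time. The Discussion gives validation against sham as an objective too, so this trade is not one the documents invite.

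The 9 points are also the top of the range, and the gain nearly vanishes if C falls midway between A and B.

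**Conclusion.** The point holds as an avoidable loss of efficiency. Validity is intact and the 80% target is met. Under the plan's own SDs and target effects, a closed test with separate variances raises A-versus-B power by about 7 points after 15% loss (82.4% to 89.2%). With a common SD of 12 the gain is 9 points. It falls to about 4–6 points if C equals B and 0–2 points if C is midway.

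These figures assume normal data, the stated SDs, a true 5-point difference and the full 15% loss. They leave out the gain from adjusting for baseline, because the documents give no correlation; that adjustment would raise power under both rules. The change is worth making because the 5-point assumption has no prior data behind it, and the extra power needs no additional patients.

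**What to change.** Before unblinding, reword the Statistical analysis section as follows:

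- Keep the omnibus treatment test at two-sided 5% as the gate. Once it is significant, test each of the three pairs at two-sided 5%, and state that this is a closed procedure for three arms.
- Use group-specific residual variances in both the gate and the pairwise tests, with degrees of freedom to match.
- Apply the same logic to the rank-based branch: each Mann–Whitney test at 5% after a significant Kruskal–Wallis test, in place of 0.017. Otherwise the two branches would follow different multiplicity rules.
- Report Tukey–Kramer simultaneous intervals alongside, and state that the closed tests decide significance.

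The cost is wording and programming only. No patient or visit is added and no contrast is given up. The downside is that the unadjusted intervals are not simultaneous, so a pair may be significant while its Tukey–Kramer interval includes zero. The text should say so in advance.

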## Methods

### Study design

This is a multicenter, three-armed, randomized controlled trial. The trial will be conducted at four hospitals in China: the Institute of Acupuncture and Moxibustion China Academy of Chinese Medical Sciences (CACMS), the Guang’anmen Hospital CACMS, the Shanghai Research Institute of Acupuncture and Meridian, and the Beijing First Hospital of Integrated Chinese and Western Medicine, between 1 March 2016 and 30 December 2017. This protocol is in accordance with the principles of the Declaration of Helsinki, and has been approved by the ethics committee of each participating hospital. Prior to enrollment, patients will give their written informed consent after acquiring detailed information of the study from the staff responsible for recruitment.

Eligible patients will be randomly assigned to receive one of the three kinds of moxibustion treatments: moxibustion using Qichun moxa floss (group A), Nanyang moxa floss (group B), or non-moxa floss (group C) for 2 weeks, and be followed up for 4 weeks (Fig. 1 and Fig. 2). Outcomes will be assessed at baseline, after a 2-week treatment and after a 4-week follow-up. This protocol has been registered at the Acupuncture-Moxibustion Clinical Trial Registry (AMCTR-IOR-16000007), a secondary register platform affiliated to the Acupuncture Clinical Trial Registration Center site and WHO International Clinical Trials Register Platform.

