### Randomization and masking

A block randomization, stratified by center, will be applied in this trial. Eligible participants will be randomly assigned to group A, B, or C with a 2:2:1 ratio. The central randomization system of the Institute of Basic Research in Clinical Medicine, CACMS will be used in this trial. The independent research assistants in each center will get a random number and group assignment by telephone or message from the system.

In this trial, moxa stick moxibustion, a type of moxibustion, will be applied. Moxa floss with Artemisia argyi leaves stored for 5 years from two habitats, Qichun County, Hubei Province, China (a habitat recognized by TCM theory and the top producer for commercially available moxa products) and Nanyang County, Henan Province, China (another top producer for commercially available moxa products), will be processed into moxa sticks named as A (Qichun moxa stick) and B (Nanyang moxa stick). For the sham control, a kind of non-moxa stick, named as C, will be made from the floss of Artemisia capillaris Thunb (a plant belonging to the same family and genus with Artemisia argyi), which presents a similar color and inflammability with moxa floss. The moxa and non-moxa sticks used in this trial will be made by the same process with the same specifications (a diameter of 1.75 cm and a length of 20 cm) and appearance, but with different labels by the same company (Nanyang Chinese Medicine Moxa LLB) (Fig. 3). The blindness effect of moxibustion using these three kinds of moxa sticks (Qichun moxa stick, Nanyang moxa stick, and non-moxa stick) has been assessed in both patients and practitioners pre-study. The results showed that patients cannot differentiate moxibustion between any of the three moxa sticks, while practitioners can differentiate non-moxa stick moxibustion from moxa stick moxibustion via brining smell, burning speed and tightness of ashes. However, they cannot distinguish moxibustion using the Qichun moxa stick from those using the Nanyang moxa stick (unpublished data). The practitioners, participants, outcome assessors, and statisticians will be kept blinded to treatment allocation throughout the trial. In this trial, emergency unblinding is not applicable.

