### Outcome measures

The primary outcome will be the change in the score on the pain subscale (pain score) of the WOMAC from baseline to week 2.

The WOMAC is a widely used disease-specific measurement for function of hip and/or knee OA [19]. It consists of 24 items divided into 3 subscales addressing severity of joint pain (5 items), stiffness (2 items) and limitation of physical function (17 items), respectively, in the previous 48 h. In this trial, a validated Chinese WOMAC [20] will be used. Each item of WOMAC will be assessed by a 100 mm visual analogue scale (VAS), with a higher score indicating worse symptom severity. Items will be summed for each subscale, resulting in possible ranges as follows: pain, 0–500 mm; stiffness, 0–200 mm and physical function, 0–1700 mm. A total WOMAC score is a sum of the scores for all three subscales, with 2400 mm being the worst possible total score.

Secondary outcomes include the change in the WOMAC pain score from baseline to week 6; the change from baseline to weeks 2 and 6 in knee pain (measured by a 100 mm VAS with higher score indicating more severe pain), the total WOMAC score, the WOMAC stiffness score, the WOMAC function score, and the patient global assessment (PGA) (measured by a 100 mm VAS with a higher score indicating a patient more greatly affected by KOA); and the responder criteria developed by the Outcome Measures in Rheumatology Arthritis Clinical Trials-Osteoarthritis Research Society International (OMERACT-OARSI) criteria [21]. The OMERACT-OARSI responders are defined as patients with (1) at least 50% improvement and an absolute change of at least 20 points in the WOMAC pain score or WOMAC function score; or (2) at least 20% improvement and an absolute change of at least 10 points in any two of the WOMAC pain score, the WOMAC function score, and the PGA.

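### Continuous secondary outcomes are analysed without a baseline covariate or a site term, although the primary model has both: a modest, avoidable loss of precision

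*Protocol article*

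**What the plan says.** The Statistical analysis section sets out three different treatments of baseline and centre.

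- **Primary outcome** (WOMAC pain change to week 2): ANCOVA with "the baseline WOMAC pain score and study site as covariates", or a Kruskal–Wallis test.
- **Binary secondary outcomes:** "binary categorical variables will be compared using the Cochran–Mantel–Haenszel method adjusted for randomization strata".
- **Continuous secondary outcomes:** the section says that "continuous variables will be assessed using ANOVA or the Kruskal-Wallis H test". Only the pairwise procedure carries over from the primary analysis. No baseline or site term is named.

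The design supplies both missing terms. The Randomization and masking section states: "A block randomization, stratified by center, will be applied in this trial". The Study design section states: "Outcomes will be assessed at baseline, after a 2-week treatment and after a 4-week follow-up".

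The continuous secondary outcomes are changes from baseline. The Outcome measures section introduces them with "Secondary outcomes include the change in the WOMAC pain score from baseline to week 6; the change from baseline to weeks 2 and 6 in" and then lists the knee-pain VAS, WOMAC total, stiffness and function, and the patient global assessment. That makes 1 + 5 × 2 = 11 outcome-by-visit analyses.

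**The concern.** The section distinguishes ANCOVA from ANOVA within a few lines, so the secondary wording reads as a chosen method rather than as detail left to an analysis plan. It is the weaker method, and no reason is given for it. As written, WOMAC pain change is modelled with baseline and site at week 2 and with neither at week 6. Centre is respected for the primary ANCOVA and the responder outcome but not for the 11 continuous analyses.

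Precision is at stake. A change score removes baseline with a fixed coefficient of one, whereas ANCOVA estimates the coefficient and leaves no more residual variance than the change score does. When randomisation is stratified by a factor that predicts outcome and the analysis omits it, the reported standard error is too large and the test is conservative.

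**Working it through.** **The plan's own figure.** The article gives no figure for secondary outcomes, so I use the A versus B calculation as a yardstick. Inputs from the Sample size section are a difference of 5, SD 12, 80% power, 5% two-sided and 15% dropout. With alpha split over three comparisons (0.05/3), n = 2 × 12² × (2.394 + 0.842)² / 5² ≈ 121 evaluable per arm. Dropout then gives 121 × 1.15 ≈ 140, or 121 / 0.85 ≈ 143. The stated 140 is reproduced. With an undivided 5% the result is 91, or 105 to 108 after dropout, which does not reproduce it.

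**Baseline as a covariate.** Let the follow-up SD be s, the baseline SD be ks and the correlation be r, the same in every group.

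- Variance of change: s²(1 + k² − 2rk)
- ANCOVA residual variance: s²(1 − r²)
- Ratio: (1 − r²) / (1 + k² − 2rk)

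The denominator minus the numerator is (k − r)², so the ratio never exceeds 1 and equals 1 when k = r. The degrees of freedom spent (one for baseline, three for four centres) are negligible against about 350 × 0.85 ≈ 297 evaluable patients.

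The article gives neither r nor k. Both are assumed here:

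| r | k = 1 | k = 0.7 |
|---|---|---|
| 0.3 | 0.91/1.40 = 0.65 | 0.91/1.07 ≈ 0.85 |
| 0.5 | 0.75/1.00 = 0.75 | 0.75/0.79 ≈ 0.95 |
| 0.7 | 0.51/0.60 = 0.85 | 0.51/0.51 = 1.00 |

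The k = 0.7 column is there because the Participants section admits only patients with a total WOMAC above 49 and at most 72 on a 0–96 scale. That window narrows the baseline spread but does not restrict follow-up.

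**In power terms (illustration only).** Take 140 × 0.85 = 119 evaluable per arm, a difference of 5, 12 read as the SD of the change, and alpha 0.05/3. The change-score analysis has 79.4% power. With k = 1, ANCOVA has 94.4%, 90.6% and 86.3% at r = 0.3, 0.5 and 0.7. With k = 0.7, the ratio at r = 0.3 is the same 0.85, hence 86.3%. At r = 0.5 the SD becomes 12 × √0.949 ≈ 11.69 and the standard error 11.69 × √(2/119) ≈ 1.516, so 5/1.516 − 2.394 ≈ 0.905, or about 81.7%. At r = 0.7 power stays at 79.4%. These inputs belong to the primary outcome; no secondary outcome is separately powered.

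**Site.** If site explains a share v of the outcome variance, adjustment multiplies the standard error by √(1 − v). Without adjustment, the true type I error at nominal 5% is 2[1 − Φ(1.96/√(1 − v))].

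| v (assumed) | SE factor | Type I error without site |
|---|---|---|
| 2% | 0.990 | 4.8% |
| 5% | 0.975 | 4.4% |
| 10% | 0.949 | 3.9% |

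**The case against.** The trial team could fairly answer as follows.

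- **Baseline is not ignored.** Every one of these outcomes is a change score. This stands: what is missing is baseline as a covariate.
- **The word ANOVA does not expressly exclude a site factor.** This is true, but the primary sentence names site and the binary sentence names the strata, so the natural reading is that the continuous analysis has neither.
- **The gain may be small.** This stands. The larger savings need equal baseline and follow-up spread, which the entry window makes doubtful, and the saving vanishes when k = r.
- **Little rides on it.** The primary ANCOVA is already adjusted, and the sample size was calculated for a one-way ANOVA, so no planned power relies on adjustment. This limits the weight of the point but gives no reason to keep the weaker method.

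Stronger readings are tempting, and the documents do not support them. A reader might infer that unadjusted comparisons are biased. Under randomisation they are unbiased on average; chance imbalance matters only conditionally, and over repeated trials it appears as variance. A reader might infer a false-positive risk, but omitting the stratification factor pushes the error rate below nominal. A reader might conclude that the week-2 and week-6 pain results cannot be compared. Both target a between-group difference in mean change; they differ in precision and in how chance imbalance is handled.

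**Conclusion.** The point holds as a matter of efficiency and consistency, for secondary outcomes only. The article names an analysis for continuous secondary outcomes that omits two adjustments it uses elsewhere and for which the data are collected.

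The variance saving from a baseline covariate runs from nothing up to 35% over the values examined (r from 0.3 to 0.7, k of 0.7 or 1, all assumed). The statement that ANOVA wastes a quarter of the patients is true only at r = 0.5 with k = 1 and should not be taken as typical. The site term adds roughly 1–5% in standard error if site explains 2–10% of variance (assumed). The calculations also take r and k as common to all groups.

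This is a free improvement: in large samples the adjusted analysis is never less precise in this setting, and it may be appreciably more precise.

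**What to change.** Replace the sentence on continuous secondary outcomes with one stating that each change score is analysed by the primary ANCOVA model: treatment as the factor of interest, with that outcome's own baseline value and study site as covariates. For WOMAC pain at week 6 the covariate is the baseline pain score already used at week 2. Keep the multiple imputation and the Tukey–Kramer pairwise procedure as they stand.

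The cost is one sentence in the protocol or analysis plan. No extra data, visits or patients are needed. The Trial status section says recruitment is under way, so the change should be dated and made before unblinding.
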